### Study population

#### Eligibility criteria

Diagnostic criteria (2): “Asian Working Group for sarcopenia: 2019 Consensus Update on Sarcopenia Diagnosis and Treatment” criteria for Possible sarcopenia, calf circumference (for men < 34 cm, for women < 33 cm), SARC-F scale ≥4 points, Handgrip strength (for men < 28 kg, for women <18 kg).

Inclusion criteria:

Conforming to the above diagnostic criteria;65 ≤ age ≤80;Gender is not limited;Be able to independently complete daily activities and basic communication, have no mental or neurological disorders, and be able to correctly understand the scale;The individual or co-residents are proficient in using smart devices such as smartphones;Voluntarily participate in the study and sign the informed consent.

Exclusion criteria:

Contraindications to exercise rehabilitation;Those with severe liver or kidney diseases;Patients with malignant tumors who are undergoing chemotherapy, radiotherapy or have bone metastases;Those who are unable to complete the exercise treatment program due to sprains, fractures, severe joint deformities, etc.Severe fracture osteoporosis with T value ≤ − 2.5SD and one or more brittle fractures at the same time.

### Recruitment

The subjects of this trial will be recruited through community promotion, hospital outpatient services, etc. The subjects are from Haidian District, Beijing, China; Taiyuan City, Shanxi Province, China; Tianjin City, China; Jining City, Shandong Province, China; Suzhou City, Jiangsu Province, China. After the researchers confirm the subjects’ willingness to participate and confirm their eligibility for inclusion, the informed consent process will be carried out. After signing the informed consent form, they will be invited to participate in the trial, and the recruitment is expected to start in April 2025 and end when 200 participants are registered.

### Baseline assessment

The researchers will collect baseline information, including participants’ general personal data and demographic information such as gender, age, history of chronic medication use, etc., and will collect all observation indicators including Handgrip strength and 30-s sit-to-stand test.

### Randomization, assignment of hiding and blinding

The randomization sequence will be generated using computer-generated random numbers, and participants will be allocated to either the intervention or control group in a 1:1 ratio. Allocation concealment will be ensured by an independent third party utilizing opaque, sealed, sequentially numbered envelopes. The randomization operation was carried out by the staff of the GCP Center of Xiyuan Hospital of China Academy of Chinese Medical Sciences. Although blinding is difficult to implement in this trial, data analysts and result evaluators will follow the blinding principles when processing the data. In addition, objective measures were chosen as the primary outcome measures in this trial to minimize measurement bias.

### Intervention protocol

#### Control group

HD, during the 12-week intervention period, subjects will receive structured health education and dietary guidance covering the etiology, pathogenesis, at-risk populations, exercise rehabilitation, and nutritional support related to sarcopenia. The educational content will systematically address the therapeutic benefits of exercise rehabilitation, along with specific implementation parameters including duration, frequency, intensity, modality selection, and safety precautions.

#### Intervention group

BHD, guidance on the basis of health education and dietary guidance, during the intervention period, the research team will implement a 12-week standardized BDJ curriculum at fixed teaching sites (comprising one 70-min centralized session weekly). The course will adopt a four-module framework: biomechanical analysis of BDJ movements, consolidation and error correction of acquired techniques, new movement instruction, and group practical guidance. Dietary education and health guidance will be systematically integrated throughout the intervention process. After completing nine BDJ foundational training (including preparatory postures), participants will advance to movement trajectory optimization and respiratory rhythm regulation phases, designed to enhance movement precision. Subjects will perform standardized home-based training using instructional videos, completing daily 30-min BDJ practice sessions (4 times/week), combined with centralized sessions to achieve a weekly training frequency of 5 sessions (1 centralized + 4 home-based). A dual-time-point video documentation protocol (pre- and post-intervention) will be employed to archive visual records for instructional standardization control and movement quality evaluation.

During the trial, no necessary routine medical treatment was ruled out for either group of subjects. If drugs such as growth estrogen and testosterone were used to improve sarcopenia, they should be reported to the researchers, and the researchers should record the medication situation of the subjects in a timely manner.

### Outcome measure

In the trial, the outcome measures will be measured before the intervention begins, after the intervention ends, and at the follow-up. All measures will be conducted by professionally trained researchers, as shown in Figure 2 for specific time points and measures.

#### Primary outcome measures

##### Handgrip strength test and 30-s sit-to-stand test

Handgrip strength test (23) is a commonly used functional assessment method in clinical practice. It measures the maximum force produced by isometric contractions of the flexor muscle groups in the forearm of the subject with a standardized handheld dynamometer, and the test results objectively reflect the functional status of the upper limb skeletal muscles and neuromuscular coordination.

30-s sit-to-stand test (24) is a standardized test for assessing lower limb functional ability, requiring subjects to complete as many sit-to-stereoscopic position changes as possible within 30 s without upper limb assistance, reflecting quadriceps muscle strength, hip flexor coordination and dynamic balance ability through counting, and is widely used in geriatric functional assessment and sports injury rehabilitation monitoring.

#### Secondary outcome measures

Muscle electrophysiological test (25): an objective examination method that quantitatively assesses motor unit recruitment patterns, neuromuscular junction conduction efficiency, and muscle excitation-contraction coupling function by recording the electrical signal characteristics of muscles at rest and contraction through surface electrodes. This technique can specifically identify neurogenic and myogenic impairments to distinguish the pathological changes of sarcopenia in old age.

Soft tissue tension (26–28): refers to the intrinsic stress characteristics of connective tissues such as skeletal muscles, fascia, and ligaments at rest, reflecting the dynamic balance between neuromuscular regulatory mechanisms and the viscoelastic properties of the tissues. Abnormal increases and decreases are significantly associated with the pathological state of muscle.

6-min walk test (6MWT) (29): a standardized submaximal exercise test for assessing cardiopulmonary reserve. By measuring the maximum distance that the subject can walk independently within a specified time, it comprehensively reflects cardiopulmonary endurance, peripheral muscle function, and self-efficacy. It is the core objective indicator for the evaluation of the therapeutic effect of cardiopulmonary rehabilitation.

Musculoskeletal ultrasound (26, 30): imaging means for visual assessment. It can precisely identify tissues such as muscles, tendons, and synovial membranes of joints, enabling measurements of muscle dimensions.

Balance function assessment (31, 32): it is often used as part of the assessment of physical function in sarcopenia patients, it is aneuromotor control test system that quantitatively assesses vestibule-visual-proprioceptive integration ability through pressure center trajectory analysis combined with dynamic posture maps. This test is crucial for evaluating the risk of falls in older adults.

Quality of life assessment (QoL) (29, 33, 34): it is a 36-item universal health-related quality of life assessment tool that quantifies an individual’s multi-dimensional health status through eight dimensions, including physical function and body pain. It has high clinical validity in the assessment of chronic disease burden.

Short Physical Performance Battery (SPPB) (35): a standardized tool for assessing lower limb function in the older population, scores through three indicators: static balance maintenance, 4-meter walking speed, and five sit-down test times. Each 1-point reduction in the total score is significantly associated with an 8–12% increase in all-cause mortality, and it has a high predictive effect in aging frailty screening.

Body composition analysis (36): a metabolic assessment technique that quantitatively evaluates body fat percentage, skeletal muscle mass index and extracellular water ratio using bioelectrical impedance analysis (BIA). It has core application value in sarcopenia screening.

### Adverse events

The common adverse events of traditional exercise training are symptoms such as chest tightness, shortness of breath, limb pain, etc. The researcher must record in detail, including the time of occurrence of adverse reactions, symptoms, signs, severity and frequency of occurrence, duration of termination, treatment methods and results, course, follow-up time, recovery date, etc. Whether treatment is needed, if so, please record the treatment given. The investigator determines whether adverse events are related to the training program and provides evidence to support that judgment. When adverse events are identified, researchers can take necessary measures based on the condition. In the event of a serious adverse event, the unit undertaking the clinical study must immediately take necessary measures to protect the patient’s safety. Record in detail the process and outcome of the treatment until it is properly resolved or the patient’s condition is stable. If a Serious Adverse Event (SAE) occurs, the investigator must report it to the research group within 24 h or no later than the second working day, and report it to the ethics committee. The investigator should sign and date the report, and record in the original data when, in what manner, and to whom the serious adverse event was reported.

### Data recording, statistics and analysis

#### Data recording

The case report form (CRF) was filled out by the investigator, and each enrolled case had to complete the CRF. All cases were observed and treated according to the study protocol, and the medical record report forms were carefully filled out in accordance with the requirements for the study medical record. The subjects’ indicators were recorded truthfully. The CRF shall be kept as the original record and shall not be altered. The original record shall not be altered when any correction is made. Only additional statements shall be used to explain the reasons, signed by the physician participating in the clinical study and dated. The completed CRFs, after being reviewed by the monitor, are handed over to the data administrator for data management.

### Statistical analysis

Data will be analyzed by independent statisticians using the SPSS 27.0 software package. The primary analysis will adhere to the intention-to-treat (ITT) principle, supplemented by per-protocol (PPS) analysis, with a two-sided *p < 0.05* defined as statistical significance. Missing data will be addressed using multiple imputation methods. Continuous variables will be described as mean ± standard deviation (SD) or median (interquartile range, IQR), and categorical variables as frequencies (percentages). Baseline characteristics between the intervention group and the control group will be compared using *independent-samples t*-tests (for normally distributed data) or *Mann–Whitney U* tests (for non-normally distributed data). Categorical variables will be analyzed using chi-square tests or Fisher’s exact tests. Primary and secondary outcomes will be evaluated using mixed-effects linear models with restricted maximum likelihood (REML). The models will include group (Baduanjin/control), time (baseline/post-intervention), and other potential confounding factors as covariates.

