### Sample size calculation

Revise it to read as follows:Sample size was calculated based on the inter-group independent sample mean comparison formula, the calculation is based on the research of Chang KV et al. (22) (The primary outcome measure was handgrip strength).Assuming a two-sided type I error (*α*) of 0.05 and a test power of 85% (type II error *β* = 0.15),it was calculated that 80 subjects were needed in each group (a total sample size of 160). Further considering a 20% dropout rate, ultimately 100 cases (200 cases in total) need to be recruited per group. Calculations were performed using G*Power software, version 3.1.9.7.

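### The listed outcome-model terms omit group-by-time, so the only treatment coefficient targets half the post-intervention difference for which the trial was sized

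*Protocol article*

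**What the plan says.** Statistical analysis states that primary and secondary outcomes will be analysed with linear mixed models fitted by REML, and gives the terms: "The models will include group (Baduanjin/control), time (baseline/post-intervention), and other potential confounding factors as covariates". It describes the outcome model nowhere else. It does not list an interaction of group with time, does not treat the baseline value as a covariate for later values, and does not say which coefficient or contrast is the treatment effect.

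Sample size calculation takes a different route: "Sample size was calculated based on the inter-group independent sample mean comparison formula". The outcome used there is handgrip strength, with two-sided alpha 0.05 and 85% power, giving 80 evaluable per group. Then: "Further considering a 20% dropout rate, ultimately 100 cases (200 cases in total) need to be recruited per group". The section points to a cited study but prints no difference, SD or standardised effect.

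Outcome measure places assessments before the intervention, after it and at follow-up. The time factor in the model sentence has only the first two.

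**The concern.** The trial asks whether the arms differ after 12 weeks of Baduanjin, having started level. A model with additive group and time terms forces the arm difference to be the same at baseline and afterwards. It has no parameter for the arms diverging. What it reports as the group effect mixes a time point at which no effect can exist with the time point of interest.

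This model serves both primary outcomes and every secondary outcome. If it is fitted as listed, the published effect would be about half the week-12 difference that readers would take it for, and a true benefit of the planned size could easily be missed. The error works towards the null. If Baduanjin has no effect, the coefficient is centred on zero, so false positives are not the issue.

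**Working it through.** **Inputs from the article (Sample size calculation; 1:1 allocation from the randomisation section).** Alpha 0.05 two-sided; power 85%; 80 evaluable per arm; 20% dropout; 100 recruited per arm.

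**Assumptions, because the article does not give them.** Standardised post-intervention effect d, back-solved below; baseline-to-post correlation ρ, shown from 0 to 0.95; equal variances at both times; complete pairs; a random intercept per participant.

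**Step 1: the plan's own figure.** It cannot be reproduced forwards without an effect size, so I inverted it. With the normal formula, d = (1.960 + 1.036) × √(2/80) = 2.996 × 0.1581 = 0.474. With the noncentral t, d = 0.477. Forwards, d = 0.475 returns 80 per arm. Dropout: 80 / (1 − 0.20) = 100, which matches.

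**Step 2: what the group coefficient estimates.** With two time points and complete balanced data, it is the arm difference in participants' two-visit averages. Its expectation is (0 + d)/2 = 0.477/2 = 0.238. This is algebra and depends on neither d nor ρ. Simulation (20,000 runs at each of ρ = 0.5 and 0.8) gave a ratio of 0.50 to the post-intervention effect.

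**Step 3: its power.** The variance is (2/n)(1 + ρ)/2, so power = Φ[(d/2)/√((2/n)(1 + ρ)/2) − 1.96]. For n = 80:
- ρ = 0: 0.2383/0.1118 = 2.132; Φ(0.172) = 56.8%
- ρ = 0.5: 0.2383/0.1369 = 1.741; Φ(−0.219) = 41.3%
- ρ = 0.8: 0.2383/0.1500 = 1.589; Φ(−0.371) = 35.5%
- ρ = 0.95: 0.2383/0.1561 = 1.527; Φ(−0.433) = 33.2%

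Simulated power was 40.8% at ρ = 0.5 and 35.2% at ρ = 0.8.

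**Step 4: comparators on the same data.** The interaction coefficient (difference in change) has variance (2/n) × 2(1 − ρ). A baseline-adjusted or common-baseline contrast has variance (2/n)(1 − ρ²).

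| ρ | Group main effect, n = 80 | Group main effect, n = 100 | Interaction, n = 80 | Baseline-adjusted, n = 80 |
|---|---|---|---|---|
| 0 | 56.8% | 66.4% | 56.8% | 85.4% |
| 0.3 | 46.4% | 55.2% | 72.2% | 88.5% |
| 0.5 | 41.3% | 49.4% | 85.4% | 93.6% |
| 0.7 | 37.3% | 44.7% | 97.3% | 98.8% |
| 0.8 | 35.5% | 42.7% | 99.7% | 99.9% |
| 0.95 | 33.2% | 40.0% | >99.9% | >99.9% |

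(85.4% rather than 85% arises from putting the t-based d into the normal formula.) The plain arm difference at the post-intervention visit, which is group plus interaction in an unconstrained model, has variance 2/n. Its power is 0.477/0.1581 = 3.015, Φ(1.055) = 85.4% at any ρ. That is the quantity the sample-size formula describes.

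**Step 5: dropout without imputation.** Additive REML fits with 100 per arm and 20% of post values missing at random (200 runs at each ρ) gave ratios of 0.42 (ρ = 0.5) and 0.41 (ρ = 0.8), with rejection rates of 35% and 30.5%. Baseline then carries more weight than the post visit. The article plans multiple imputation, which would restore balance and bring the ratio back to about one half if the imputation model lets the arms differ after baseline.

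**The case against.** The strongest reply is that this is a journal article. Its sentence names what the models include; it does not say main effects only, and it leaves the confounders open. A plan that names both group and time for repeated measures may be shorthand for a model with their interaction, with the tested contrast set out in a fuller document. A reader might infer from the sentence that the interaction has been ruled out, or that the additive model will certainly be run. The article establishes neither, and that part of the reply stands.

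It does not remove the point. The sentence does more than stay silent: it lists the terms and spells out the levels of both factors, with baseline as one of them. An analyst who entered those terms would obtain Step 2's coefficient, and no other listed term could carry the treatment effect. If a fuller plan has the interaction, the published sentence misdescribes the primary analysis.

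A second reply concerns size. A reader might take the values at ρ = 0.5 to 0.8, about 36 to 41%, as the trial's power. They need a back-solved d, a correlation found nowhere in the article, and 80 complete pairs. With all 100 per arm complete, the range over ρ from 0 to 0.95 is 66% down to 40%.

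Third, a reader might credit the whole gap to the baseline-adjusted column to the missing term. Part of it comes from a more efficient estimator. The ordinary interaction coefficient does no better than the main effect at ρ = 0 and reaches 85% only at about ρ = 0.5.

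**Conclusion.** The point holds for the model as written. The halving of the estimate follows from the listed terms and randomisation, with balanced data and no outside figure. The loss of power is conditional. With 80 complete pairs per arm, equal variances and d of about 0.477, power for the group coefficient runs from 57% down to 33% over ρ from 0 to 0.95, and stays below 85% throughout; the same is true with 100 complete per arm. No single power figure can be drawn from the article, and the article does not show that the full plan lacks the interaction. What it does show is that its only statement of the primary model has no term for the difference on which the sample size rests. That sentence should be corrected before the data are analysed.

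**What to change.** Rewrite the model sentence along these lines: *Fixed effects are group, time as a categorical factor (baseline, post-intervention, follow-up), group-by-time and the planned covariates. The treatment effect is the arm difference at the post-intervention visit.*

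Preferably, constrain the arms to a common baseline mean, or use the post-baseline values as responses with the baseline value as a covariate. Either keeps the same target and gains precision as ρ rises. This is a recommendation; adding the interaction and naming the contrast is enough to repair the defect. Adding follow-up as a level of time brings the model into line with the Outcome measure section, and naming the visit prevents the effect from being averaged over visits again.

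If the full plan already specifies this, only the published sentence needs changing to match. The cost is wording: no new data, no change in sample size, and the same mixed-model procedure in the named software.

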### Dissemination

The study protocol is in line with the *Declaration of Helsinki* and is available through the International Traditional Medicine Clinical Trial Registry (itmctr.ccebtcm.org.cn). The results of the study will be published in a peer-reviewed scientific journal or at a local, national or international conference. The results of the study will also be shared directly with all participants and disseminated to researchers, health service providers, health care professionals and the general public through courses, presentations and the Internet.

## Discussion

BDJ, as a traditional body and mind exercise of light to moderate intensity, is designed to emphasize symmetry, coordination and breathing regulation, which can effectively activate the core muscles and promote the balanced development of muscles throughout the body (37–40). In addition, the low-intensity nature of BDJ makes it more suitable for older adults with reduced muscle mass and weakened muscle strength (41),reducing the risk of sports injuries while improving exercise compliance (42).

In terms of observation indicators, we not only selected the classic screening and diagnostic indicators for sarcopenia in older adults (43), but also selected more refined indicators including exercise endurance, balance function, subjective scales, etc. To comprehensively evaluate the rehabilitation effect of BDJ on older adult patients with sarcopenia. In order to provide clinical evidence for the rehabilitation of sarcopenia in older adults under the guidance of traditional exercises in the future.

This study plans to explore the intervention effect of BDJ exercise on older adult patients with sarcopenia through a randomized controlled trial (RCT). However, this study also has some limitations. Firstly, although we managed to control bias as much as possible through randomization and blinding design, due to the particularity of the exercise intervention, complete blinding could not be carried out on the participants and the intervention implements, which might have had some impact on the results. Secondly, other daily activities of the participants during the intervention were difficult to monitor completely, and the intensity of their activities could not be precisely quantified. Nevertheless, the findings of this study will still have significant clinical and public health implications. BDJ, as a traditional exercise that is easy to learn and promote, can provide a safe and effective non-pharmaceutical intervention for older adults in the community, especially those with sarcopenia (44). Future studies could further expand the sample size, extend the intervention period, and explore the combined effects of BDJ with other interventions, such as nutritional supplementation and resistance training, in order to provide a more comprehensive scientific basis for the prevention and treatment of sarcopenia in older adults.

In conclusion, this trial will provide preliminary evidence of the effectiveness of BDJ exercise in improving muscle mass and physical function in older adults patients with sarcopenia, supporting its wide application in the health management of older adults in the community.
